### Plans to promote participant retention and complete follow-up {18b}

The study team will provide reminders to study subjects prior to the vaccination visit and their follow-up visits. Study subjects will be reimbursed regularly for their time and transportation costs at every study visit.

### Data management {19}

Data for each study applicant should be reported in a case record form (CRF). All study data will be recorded and stored in an electronic format (eCRF). All data entries are checked and monitored by the sponsor and the study site. Clinical study data, including safety data as well as laboratory data and immunogenicity data, should be written in a source document and recorded in an eCRF. Safety data will include physical examination, medical history, AEs, SAEs, reactogenicity data, and diary information. The Investigator is responsible for verifying that data entries for all study participants are accurate and correct by physically or electronically signing the eCRF.

The data will be collected in a secure system and saved using an electronic data capture (EDC) system that enables password protection. The eCRF is integrated into the Rave, Medidata EDC system through a secure website that utilizes cloud access for enhanced efficiency and controlled accessibility of the clinical study. The Sponsor is responsible for the data management of this study, including quality checks of the data as well as data protection.

This study will be conducted in compliance with ICH CGP guidelines and in accordance with the most recent version of the Declaration of Helsinki. Records and documents, including signed ICFs, pertaining to the conduct of this study must be retained by the Investigator for 25 years after study completion unless local regulations or institutional policies require a longer retention period. The Sponsor, which is designated as the data controller, will confirm compliance of the GDPR Regulation (EU) 2016/679 throughout all stages of study data management.

### Confidentiality {27}

All subject data, clinical documents, and study findings will be considered confidential. The study site will collect, process, and store subject data according to the site's data protection and privacy policy and in compliance with applicable laws and regulations governing the processing of personal data. The Sponsor, investigator, and other study personnel must not disclose information prior to written approval from the Chief Principal Investigator.

### Plans for collection, laboratory evaluation, and storage of biological specimens for immunogenicity analysis {33}

Humoral and cellular immune responses elicited after COVID-19 vaccine candidate administration will be evaluated. Approximately twenty (19) ml of blood will be taken from each subject during Visit 1, Visit 4, and Visit 5. A total of 60 ml of blood will be collected for immunogenicity assessment throughout the study. Blood must be drawn prior to administration of the investigational vaccine. An optional blood draw of −50 ml will be taken at Visit 5 (from selected participants who consent) for exploratory COVID-19 research. All immunogenicity testing will be performed at accredited central laboratories and by qualified staff.

### Immunogenicity assessment

#### Humoral immune response

Approximately 4 ml of whole blood will be taken during Visit 1, Visit 4, and Visit 5. The blood must be drawn prior to vaccination of the subjects. The serum should be separated from the whole blood prior to conducting humoral antibody response assessments.

The humoral immune response will be evaluated as follows:

Binding antibody responses to the S.FL, S1, and RBD S1 of wild-type SARS-CoV-2 using ELISA.Binding antibody response to the S.FL of SARS-CoV-2 variants of concern using V-plex COVID-19 panel.Neutralizing antibody directed against wild-type SARS-CoV-2 using V-plex assay COVID-19 (ACE2) neutralizing assay kit.Neutralizing antibody directed against SARS-CoV-2 variants of concern using V-plex COVID-19 panel.

Antibody response to the spike protein of SARS-CoV-2 will be evaluated for all subjects by measurement of the bAB and nAB responses as follows:

##### Binding antibodies

Assessment of bAB responses directed against S.FL, S1, and RBD of wild-type SARS-CoV-2 at Visit 1, Visit 4, and Visit 5.

Assessment of bAB responses directed against S.FL of SARS-CoV-2 variants of concern at Visit 1, Visit 4, and Visit 5.

##### Neutralizing antibodies

Assessment of nAB responses against wild-type SARS-CoV-2 at Visit 1, Visit 4, and Visit 5.

Assessment of nAB responses against SARS-CoV-2 variants of concern at Visit 1, Visit 4, and Visit 5.

#### Cellular immunity assessment

Cellular immunity will be evaluated in all recruited subjects. Approximately 16 ml of blood will be taken from each subject during Visit 1, Visit 4, and Visit 5. The blood should be drawn prior to vaccination of the subjects. Peripheral blood mononuclear cells (PBMCs) will be collected for the assessment of cell-mediated immunity using intracellular cytokines staining.

## Statistical methods

### Statistical methods for primary and secondary outcomes {20a}

#### Safety and tolerability endpoints and analysis

Safety and tolerability data will be evaluated using descriptive summary statistics for local reactions, systemic events, AEs/SAEs, and abnormal hematology and chemistry laboratory parameters, for each vaccine cohort. The sympotoms and corresponding grades for local AE, SAE, and other adverse events are categorized based on ICH E2A definitions and NCI Common Terminology Criteria for Adverse Events (CTCAE) and are summerized in Tables 4–6, respectievely.

**Table 4 T4:** Local adverse events at administration site (i.e., reactogenicity).

Symptom/Sign	Grade 1	Grade 2	Grade 3	Grade 4
Pain	Pain or tenderness causing no or minimal limitation of use of limb	Pain or tenderness causing greater than minimal limitation of use of limb	Pain or tenderness causing inability to perform usual social & functional activities	Pain or tenderness causing inability to perform basic self–care function OR Hospitalization indicated
Rash/Redness	2.5 to < 5 cm in diameter OR 6.25 to < 25 cm^2^ surface area AND Symptoms causing no or minimal interference with usual social & functional activities	≥5 to < 10 cm in diameter OR ≥ 25 to < 100 cm^2^ area OR Symptoms causing greater than minimal interference with usual social & functional activities	≥10 cm in diameter OR ≥100 cm^2^ surface area OR Ulceration OR Secondary infection OR Phlebitis OR Sterile abscess OR Drainage OR Symptoms causing inability to perform usual social & functional activities	Potentially life– threatening consequences (e.g., abscess, exfoliative dermatitis, necrosis involving dermis or deeper tissue)
Induration/Swelling	2.5 to < 5 cm in diameter or 6.25 to < 25 cm^2^ surface area AND Symptoms causing no or minimal interference with usual social & functional activities	≥5 to < 10 cm in diameter OR ≥25 to < 100 cm^2^ area OR Symptoms causing greater than minimal interference with usual social & functional	≥10 cm in diameter OR ≥10 cm^2^ surface area OR Ulceration OR Secondary infection OR Phlebitis OR Sterile abscess OR Drainage OR Symptoms causing inability to perform usual social & functional activities	Potentially life–threatening consequences (e.g., abscess, exfoliative dermatitis, necrosis involving dermis or deeper tissue)

**Table 5 T5:** Adverse events at non–injection site (systemic).

Symptom/Sign	Grade 1	Grade 2	Grade 3	Grade 4
Vomiting	Transient or intermittent AND No or minimal interference with oral intake	Frequent episodes with no or mild dehydration	Persistent vomiting resulting in orthostatic hypotension OR Aggressive	Life–threatening consequences (e.g., hypotensive shock)
Diarrhea	Transient or intermittent episodes of unformed stools OR Increase of ≤ 3 stools over baseline per 24–h period	Persistent episodes of unformed to watery stools OR Increase of 4 to 6 stools over baseline per 24–h period	Increase of ≥7 stools per 24–h period OR IV fluid replacement indicated	Life–threatening consequences (e.g., hypotensive shock)
Fever (temperature in °C)	38.0– < 38.6	38.6– < 39.3	39.3– < 40.0	≥40.0
Nausea	Transient (< 24 h) or intermittent AND No or minimal interference with oral intake	Persistent nausea resulting in decreased oral intake for 24 to 48 h	Persistent nausea resulting in minimal oral intake for > 48 h OR Rehydration indicated (e.g., IV fluids)	Life–threatening consequences (e.g., hypotensive shock)
Abnormal skin mucous membranes	Erythema, pruritus, color change	Diffuse rash, maculopapular rash, dry, desquamation	Bleb, effusion, desquamation, ulceration	Exfoliative dermatitis involves mucous, or polymorphic erythema, or is suspected of Stevens–Johnsons syndrome
Acute allergic reaction	Localized urticaria (wheals) with no medical intervention indicated	Localized urticaria with intervention indicated OR Mild angioedema with no intervention indicated	Generalized urticaria OR Angioedema with intervention indicated OR Symptoms of mild bronchospasm	Acute anaphylaxis OR Life–threatening bronchospasm OR Laryngeal edema
Fatigue, tiredness	Symptoms causing no or minimal interference with usual social & functional activities	Symptoms causing greater than minimal interference with usual social & functional activities	Symptoms causing inability to perform usual social & functional activities	Incapacitating symptoms of fatigue or malaise causing inability to perform basic self–care functions

**Table 6 T6:** Other adverse events—general principles for classification of adverse events.

Grade 1	Grade 2	Grade 3	Grade 4	Grade 5
Mild: short duration (< 48h) or mild discomfort, causing no interference with daily life with no medical intervention indicated	Moderate: causing mild or moderate limitation of use of limb, with no or mild medical intervention indicated	Severe: causing greater than minimal limitation of use of limb, with medical intervention or hospitalization indicated	Critical: may be life–threatening, causing severe limitation of use of limb, with intensive hospitalization indicated	Death

The safety and toelrabilty analyses will be evaluated as follows:

Assessment of administration site reactions (local reactions, i.e., reactogenicity)—frequency of local solicited AEsAssessment of systemic AEs—frequency of systemic solicited AEsClinical assessment of participants' general health statusClinical laboratory investigations [hematology, clinical chemistry, urinalysis, and pregnancy tests (female participants)]—percentage of participants with clinically significant abnormal hematology and chemistry laboratory values at 1 and 7 days after Visit 1; and 30 days after Visit 1; percentage of participants with graded shifts in hematology and chemistry laboratory assessments between Visit 1 and 1 and 7 days after Visit 1; and 30 days after Visit 1.Monitoring of participants' COVID-19 infection status.Recording of unsolicited AEs and SAEs—reactogenicity to the vaccine will be assessed based on the percentage and frequency of AEs up to 7 days after receiving a study vaccine dose. The percentage of subjects experiencing unsolicited AEs up to 30 days after receiving a study vaccine will also be determined.Recording of concomitant medication useAEs and SAEs will be collected from the first administration of the investigational vaccine until study completion.

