#### Stopping rules

The stopping rules will be applied based on AEs, SAEs, clinical laboratory assessments, and diary card data. These data will be monitored by the investigator and sponsor for the purpose of identifying possible risk.

The following are considered as stopping/pausing rules in this Phase 1 study:

A participant receiving the investigational vaccine (in any cohort) who develops Grade 4 AEs or laboratory abnormalities that are assessed by the investigator as possibly related to the vaccine with no other alternative or plausible causes. Vaccination will be stopped until a full safety review is completed.Two or more participants receiving the investigational vaccine (in any cohort) who develop Grade 3 AEs or laboratory abnormalities after vaccination that are assessed by the investigator as possibly related to the vaccine with no other alternative or plausible causes. Vaccination will be stopped until a full safety review is completed.A participant receiving the investigational vaccine (in any cohort) develops a fever (>40°C) for more than 24 h after receiving the vaccine with no other alternative or plausible causes. Vaccination will be stopped until a full safety review is completed.If a participant in any cohort requires admission to an intensive care unit (ICU) for COVID−19 infection after receiving the investigational vaccine that is assessed as possibly related to the vaccine with no other plausible or attributable causes. Vaccination will be stopped until a full safety review is completed.A participant receiving the investigational vaccine (in any cohort) who develops a SAE that is assessed by the investigator as possibly related to the vaccine with no other alternative or plausible causes. Vaccination will be stopped until a full safety review is completed.A participant receiving the investigational vaccine (in any cohort) who develops a serious adverse reaction that is assessed by the investigator as possibly related to the vaccine with no other alternative or plausible causes. Vaccination will be stopped until a full safety review is completed.Two or more participants receiving the investigational vaccine (in the same cohort) who develop severe non-serious adverse reactions, whether or not they are within the same organ class.If a participant in any cohort dies and this is aassessed by the investigator as possibly related to the investigational vaccine. In this case, all vaccination will be halted.

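### Table 4 gives the Grade 3 swelling area as ≥10 cm² where its own pattern gives ≥100 cm², so two related swellings about 3.2 cm across would meet the Grade 3 stopping rule

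*Protocol article*

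**What the plan says.** Table 4 (Statistical methods {20a}, Safety and tolerability endpoints and analysis) grades local reactions by diameter, surface area or effect on activities. For Induration/Swelling the Grade 3 cell reads "≥10 cm in diameter OR ≥10 cm^2^ surface area OR Ulceration OR Secondary infection", followed by further alternatives, all joined by OR.

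The Rash/Redness row directly above has the same structure. Its Grade 1 is "2.5 to < 5 cm in diameter OR 6.25 to < 25 cm^2^ surface area AND Symptoms causing no or minimal interference", its Grade 2 is "≥5 to < 10 cm in diameter OR ≥ 25 to < 100 cm^2^ area" or a symptom criterion, and its Grade 3 is "≥10 cm in diameter OR ≥100 cm^2^ surface area OR Ulceration OR Secondary infection". The Grade 1 and Grade 2 size bands in the Induration/Swelling row carry the same numbers as these. The two rows differ in size limits only at the Grade 3 area.

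Under Stopping rules (Adverse events reporting and harm {22}), one trigger is "Two or more participants receiving the investigational vaccine (in any cohort) who develop Grade 3 AEs or laboratory abnormalities after vaccination", provided the investigator judges the events possibly related and sees no other plausible cause. Vaccination then stops until a full safety review is done. The rule sets no size criterion of its own and does not exempt local reactions. Tables 4 to 6 are the only severity grading the article gives.

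**The concern.** A severity scale has to place each event in one grade. As printed, the Grade 3 area limit for swelling lies inside the Grade 1 band, and every area in the Grade 2 band also exceeds it. Two assessors could apply the table correctly to the same swelling and record different grades.

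This would be a minor blemish if the grades were only descriptive, but Grade 3 is an operating threshold. Two vaccine recipients with related Grade 3 events, counted across all cohorts, are enough to stop vaccination. Swelling at the injection site is listed in the Risk and mitigation section as a risk of any vaccination, and an investigator will usually attribute it to the injection. The stake is a needless halt in a first-in-human escalation, triggered by reactions the same table also calls Grade 1 or Grade 2. Any tabulation of swelling by grade, within a primary endpoint that includes local reactions, would be ambiguous as well.

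**Working it through.** **Inputs.** The size limits come from the two rows of Table 4. The trigger of two or more vaccine recipients comes from Stopping rules. The cohort size of 14 and the 3:1 allocation come from Intervention description {11a}.

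**Step 1: the table's rule.** The area limits follow area = diameter².

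| Lower diameter limit | Diameter² | Rash/Redness area limit | Induration/Swelling area limit |
|---|---|---|---|
| 2.5 cm (Grade 1) | 6.25 cm² | 6.25 | 6.25 |
| 5 cm (Grade 2) | 25 cm² | 25 | 25 |
| 10 cm (Grade 3) | 100 cm² | 100 | **10** |

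The rule reproduces five of the six lower limits, and the upper end of Grade 2 (<10 cm, <100 cm²) in both rows. Only the Grade 3 swelling area fails. A circular area, πd²/4, gives 4.9, 19.6 and 78.5 cm². That reproduces none of the printed limits, so it cannot explain the 10 either.

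**Step 2: size of the discrepancy.** 100/10 = 10, so the printed limit is one tenth of the implied one. On the table's rule, 10 cm² corresponds to √10 = 3.16 cm. For a circle it is 2√(10/π) = 3.57 cm. Both lie in the Grade 1 diameter band of 2.5 to <5 cm, although the same cell sets its diameter limit at 10 cm.

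**Step 3: overlap of the bands.**
- Grade 1 area band also meeting Grade 3: (25 − 10)/(25 − 6.25) = 15/18.75 = 80%.
- Grade 2 area band also meeting Grade 3: (100 − 25)/(100 − 25) = 100%.
- Both together: (100 − 10)/(100 − 6.25) = 90/93.75 = 96%.

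These are shares of the area scale. They are not shares of expected events.

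**Step 4: reaching the stopping rule.** With 14 × 3/4 = 10.5, each cohort has 10 or 11 vaccine recipients, so n is 30 to 33 over three cohorts. The documents give no swelling rate, so p below is an assumption: the share of vaccine recipients with a related swelling of at least 10 cm². The chance of two or more is 1 − (1 − p)ⁿ − np(1 − p)ⁿ⁻¹.

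| Assumed p | n = 30 | n = 33 |
|---|---|---|
| 2% | 12% | 14% |
| 5% | 45% | 50% |
| 10% | 82% | 86% |

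The table shows how sensitive the rule would be under literal grading. It does not predict how often a pause would occur.

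**The case against.** The best case on the other side is that this is a visible slip of one digit. The neighbouring Grade 2 cell ends at <100 cm², the diameter in the same cell is 10 cm and the row above prints 100, so a careful grader would see what was meant. Diameter is an equal alternative throughout and gives consistent grades. A false pause needs several things together: grading by area, choosing the literal Grade 3 limit over the lower grade that also fits, two different vaccine recipients, and a judgement that both events are related. The error is also conservative, since a pause leads to a review in which the actual sizes would be seen. Finally, the article has many copy errors. A zero may have been lost in typesetting, and the full protocol and the case report form are not at hand.

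Most of this stands, and it limits the weight of the point. The intended value is not in doubt, no harm can be concealed, and the documents do not show that a false pause is likely. Swellings near the top of the affected range, just under 10 cm across on the table's rule, are not small either.

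None of it makes the printed value right. No section of the article corrects it, and a condensed article may omit detail but should not state a wrong threshold. A table that feeds a stopping rule should not rely on staff noticing the mistake.

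**Conclusion.** The concern holds. The Grade 3 area limit for induration/swelling is wrong as written: 10 cm² in place of 100 cm². It conflicts with the row's own Grade 1 and Grade 2 bands, with the diameter in the same cell and with the row above. Swellings of 10 to <25 cm² with minimal symptoms are both Grade 1 and Grade 3, and those of 25 to <100 cm² are both Grade 2 and Grade 3. Two such swellings in different vaccine recipients, judged related with no other plausible cause, would stop vaccination.

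That consequence assumes that area is used and the printed limit is applied literally, and that Tables 4 to 6 supply the grades for the stopping rule. The percentage of participants with any local reaction is unaffected. The point should be fixed. It does not threaten participant safety or bias the primary summaries of overall frequency.

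**What to change.** Change the Grade 3 surface area for Induration/Swelling in Table 4 to ≥100 cm². This continues the Grade 2 band, matches the 10 cm diameter and agrees with the Rash/Redness row. Check the full protocol, the electronic case report form and any diary grading text, and make the same change wherever the printed value appears. If swellings have already been graded, confirm that none of 10 to <100 cm² was recorded as Grade 3 on area alone.

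The cost is one number in the protocol text, and the same number in the form or diary text if it was copied there. The design, sample size and analysis do not change.

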## Assignment of intervention: allocation

### Randomization {16}

When an individual is determined to be eligible to participate in the study, the subject will be enrolled in a computerized randomization system that assigns a designated subject ID to allocate them to receive either the COVID-19 pDNA vaccine or placebo using Interactive Response Technology (IRT). Each cohort will contain 14 subjects. At Visit 1, the first two subjects of each cohort will be randomized according to a separate randomization list. One subject will be randomized to placebo, and one subject will be randomized to the study treatment to ensure that at least one subject will receive the study vaccine. They will be monitored for 4 h, with each subject to be monitored for 60 min before proceeding to the next subject. The next four participants in each cohort will be vaccinated at least 48 h after the first 2 participants complete their visit 2 safety data review. They will also be observed for at least 4 h at the study site. Vaccination of the rest of the subjects in each cohort will commence no sooner than 24 h after the sixth participant has undergone vaccination. All subjects in the dosing visit (Visit 1) will be observed for 4 h.

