## Oversight and monitoring

### Composition of data monitoring committee {5d}

A DMC by Icon plc will be implemented for this Phase 1 COVID-19 vaccine trial for the purpose of reviewing the safety data of participants during their periodic visits. The role of the DMC is to review safety data as described in the DMC charter. Escalation between doses will be based on DMC review. Dose escalation will start at least 12–14 days after the previous cohort received the study vaccine for (Cohort 1 and Cohort 2) and (Cohort 2 and Cohort 3).

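### Table 5 prints desquamation without a qualifier under both Grade 2 and Grade 3, so isolated dry peeling may or may not count toward the two-participant Grade 3 pause rule

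*Protocol article*

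**What the plan says.** The section on safety and tolerability endpoints (Statistical methods {20a}) bases its grading on ICH E2A and CTCAE and says that Tables 4 to 6 summarise it. Table 5 covers systemic events. For its skin and mucous membrane row:

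- Grade 2: "Diffuse rash, maculopapular rash, dry, desquamation"
- Grade 3: "Bleb, effusion, desquamation, ulceration"
- Grade 4: exfoliative dermatitis involving mucosa, polymorphic erythema, or suspected Stevens-Johnson syndrome.

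The grade feeds the section Stopping rules. One rule there reads: "Two or more participants receiving the investigational vaccine (in any cohort) who develop Grade 3 AEs or laboratory abnormalities after vaccination". The events must also be judged possibly related, with no other plausible cause. Grade 2 events do not enter this rule.

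Other safeguards apply:

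- one vaccinee "who develops Grade 4 AEs or laboratory abnormalities that are assessed by the investigator as possibly related to the vaccine"
- one vaccinee "who develops a SAE that is assessed by the investigator as possibly related to the vaccine"
- "Two or more participants receiving the investigational vaccine (in the same cohort) who develop severe non-serious adverse reactions"
- for dose escalation, "Escalation between doses will be based on DMC review" (Composition of data monitoring committee {5d}).

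**The concern.** A grading table that feeds a pause rule should give one grade to one finding. Here the same unqualified sign appears in two adjacent cells, and the boundary between them is the one that the rule uses. Two graders who both follow the printed table could record the same isolated peeling as Grade 2 or as Grade 3. Whether vaccination pauses could then depend on which cell was read. The article describes the product as not previously tested in people, so this is a poor place for an avoidable ambiguity. Any tabulation of systemic events by grade could differ in the same way, but the pause rule is the main matter.

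**Working it through.** The article states no figure on this point, so there is none to reproduce. The check compares the cells and then counts.

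**1. Overlap of the cells.**
- Grade 2 terms: diffuse rash, maculopapular rash, dry, desquamation.
- Grade 3 terms: bleb, effusion, desquamation, ulceration.
- Common to both: desquamation only.

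**2. Does a kinder reading remove it?** Suppose the comma in the Grade 2 cell is stray and the intended sign is dry desquamation. The Grade 3 term still has no qualifier, so dry peeling meets both cells. The overlap narrows but does not close. Peeling together with bleb, effusion or ulceration is Grade 3 on those signs and is not affected.

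**3. Is there a tie-break?** Most other rows of Table 5 separate Grades 2 and 3 by stool count, temperature, duration or function. The skin row uses names of signs only, so a repeated name leaves nothing to decide by. Neither the text around Tables 4 to 6, nor Adverse events reporting and harm {22}, nor Stopping rules says which grade applies when two cells fit.

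**4. Effect on the count (threshold 2 vaccinees, all events judged related).**

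| Situation | Peeling read as Grade 2 | Peeling read as Grade 3 |
|---|---|---|
| One isolated case only | 0, no pause | 1, no pause |
| Two isolated cases in two vaccinees | 0, no pause | 2, pause |
| One isolated case plus one clear Grade 3 event in another vaccinee | 1, no pause | 2, pause |

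**5. Who could contribute while a pause still matters?** Intervention description {11a} gives 14 subjects per cohort at 3:1. Randomization {16} puts the first two of each cohort on a separate list: "One subject will be randomized to placebo, and one subject will be randomized to the study treatment".
- Cohorts 1 and 2, 3:1 applied to everyone: 2 × 14 = 28, and 28 × 3/4 = 21 vaccinees. Per cohort this is 14 × 3/4 = 10.5, which is not a whole number.
- Cohorts 1 and 2, 1:1 first pair and then 3:1 among the other 12 (an assumption): 1 + 12 × 3/4 = 10 per cohort, so 20 vaccinees.
- Cohort 3 before its last batch: 2 + 4 = 6 subjects. One of the first two receives placebo, so at most 1 + 4 = 5 are vaccinees. Then 14 − 6 = 8 subjects remain to be dosed.

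The article gives no rate for this sign, so no probability of a missed or extra pause is calculated.

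**The case against.** **Cell context.** Grade 2 groups the sign with rash and dryness, and Grade 3 with blistering and open skin. An experienced grader would probably read dry peeling in the first and peeling with skin breakdown in the second. This stands in part: it narrows the ambiguity, but the grader has to supply the distinction.

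**Lost or condensed text.** Other cells look cut short, such as Grade 3 vomiting in Table 5 and Grade 2 swelling in Table 4, and an article condenses the full protocol. A qualifier may exist elsewhere. The Grade 3 skin cell does not itself look truncated, but the point is established only for the printed article.

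**Other guidance.** Table 6 separates grades by limitation and intervention, but it is headed as covering other adverse events, so it is no tie-break for a sign that Table 5 lists. One could also argue that the tables already imply taking the highest grade, since some Table 4 entries overlap as well. Applied to this row, that would leave the Grade 2 entry for desquamation with no use, so it can hardly be the intent.

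**Little consequence.** This largely stands. The pause needs two vaccinees with related events, the peeling must be isolated, and dosing must still be under way. Other rules catch the worse cases. One qualification is that Table 6 labels Grade 3 as severe. If the severe non-serious rule is read that way, the same ambiguity enters it. That rule also needs both cases in one cohort, whereas the Grade 3 rule pools cohorts.

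**Stronger readings.** A reader might infer that the Grade 3 pause rule does not work, or that serious skin toxicity could go unnoticed. The documents do not support either. The rule is clear for other Grade 3 events, the Grade 4 cell and the serious event rule each act on a single related case, and the DMC reviews safety data before each escalation.

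**Conclusion.** The inconsistency is real as printed: isolated desquamation, above all dry peeling, fits both Grade 2 and Grade 3, and nothing in the article settles which applies. It can change whether the two-participant Grade 3 rule is met, but only in the two situations shown in the count table. What remains uncovered is mainly non-serious peeling that is not judged severe, or severe cases split across cohorts.

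The practical size is small. That the sign is rare is a judgement, not a figure from the article. The range of 20 to 21 vaccinees in Cohorts 1 and 2 depends on how the 12 subjects after the first pair are allocated. This is a minor correction worth making, not a threat to the design.

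**What to change.** Before first dosing, edit the Table 5 skin row so that the two cells do not overlap. For example:

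- Grade 2: diffuse or maculopapular rash; dry, limited desquamation.
- Grade 3: moist or extensive desquamation, bleb, effusion or ulceration.

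The sponsor's clinicians should settle the exact wording for type and extent. The cost is one table row, carried into the grading instructions used at the site.

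Do not solve it with a blanket rule that the highest fitting grade applies, because trivial dry peeling would then count toward a pause. Applied across the tables, such a rule would also act on the Grade 3 swelling entry in Table 4, printed as 10 cm² or more. Swelling of 10 to under 100 cm² would become Grade 3, although the Grade 2 cell runs from 25 to under 100 cm². Do not move all isolated desquamation to Grade 2 either, since moist or extensive peeling should still count.

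### Table 6, the protocol's general severity scale, overlaps at Grades 2 and 3 and has no literal grade for treated non-limb events, yet its grades feed the stopping rules

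*Protocol article*

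**What the plan says.** All grading tables are in the protocol article, Statistical methods {20a}. Table 6 is captioned "Other adverse events—general principles for classification of adverse events". Its levels are:

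- Grade 1: brief or mildly uncomfortable, "causing no interference with daily life with no medical intervention indicated".
- Grade 2: "Moderate: causing mild or moderate limitation of use of limb, with no or mild medical intervention indicated".
- Grade 3: "Severe: causing greater than minimal limitation of use of limb, with medical intervention or hospitalization indicated".
- Grade 4: possibly life-threatening, with severe limb limitation and intensive hospital care.
- Grade 5: death.

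In Table 4, Grade 2 injection-site pain is "Pain or tenderness causing greater than minimal limitation of use of limb". In the skin and mucous membrane row of Table 5, Grade 2 is "Diffuse rash, maculopapular rash, dry, desquamation" and Grade 3 is "Bleb, effusion, desquamation, ulceration".

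The text introducing the tables says grading is based on ICH E2A and CTCAE. Table 1 (Risk-benefit assessment) refers to FDA guidance for toxicity grading.

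The Stopping rules section counts "Two or more participants receiving the investigational vaccine (in any cohort) who develop Grade 3 AEs or laboratory abnormalities after vaccination" when the investigator judges them possibly related with no other plausible cause. One Grade 4 event under the same condition also stops vaccination. A further rule counts two or more severe non-serious reactions in the same cohort.

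**The concern.** A severity scale should be ordered, its levels should exclude one another, and it should apply to the events it is meant to grade. Table 6 falls short in two ways.

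First, on the limb criterion Grade 3 begins below the top of Grade 2, and its wording is what Table 4 uses for Grade 2 pain. The treatment criterion does not fully separate the two levels, because mild medical intervention is also medical intervention.

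Second, limb use is a natural measure for an injected arm but not for events elsewhere in the body. The Risk and mitigation section names headache and chills among the expected systemic events, and neither has a row in Table 5 as shown. They fall to Table 6, where Grades 2 to 4 ask about a limb.

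At stake is whether the Grade 3, Grade 4 and severe-reaction triggers respond to the same event in the same way whoever grades it. In a first-in-human dose escalation with a two-participant trigger, few gradings are needed to change the outcome.

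**Working it through.** The plan states no event rate or operating characteristic for the Grade 3 rule, so there is no figure to reproduce. Two checks apply.

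**1. Literal reading of Table 6.** Assumptions: the limb clause and the treatment clause must both hold; mild and moderate both exceed minimal; mild medical intervention is a kind of medical intervention. Each cell shows the grades met, and a dash means none.

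| Limb limitation | No intervention | Mild | Medical | Hospitalization | Intensive hospitalization |
|---|---|---|---|---|---|
| None | 1 (if daily life is undisturbed) | – | – | – | – |
| Mild | 2 | 2 and 3 | 3 | 3 | 3 |
| Moderate | 2 | 2 and 3 | 3 | 3 | 3 |
| Severe | – | 3 | 3 | 3 | 3 and 4 |

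Minimal limitation is left out, because its result depends on whether it counts as no interference or as mild.

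- Two cells meet both Grade 2 and Grade 3: mild or moderate limitation with mild intervention.
- Moderate limitation with ordinary medical intervention meets only Grade 3, the level labelled severe, although the Grade 2 limb clause names moderate limitation.
- With no limb limitation, four of the five cells fit no grade. A headache that disturbs daily life and needs treatment fails both Grade 1 conditions and the limb clause of Grades 2 to 4.
- Severe limitation without intervention also fits no grade.
- If mild is taken to mean minimal, the Grade 2/3 overlap shrinks to one cell (moderate limitation, mild intervention) but remains.

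These are counts of definitions. The cells are not equally likely, and they say nothing about frequency.

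**2. Sensitivity of the two-participant trigger (illustration only).** Each cohort has 14 subjects at 3:1 (Intervention description {11a}): 14 × 3/4 = 10.5, so 10 or 11 vaccinees per cohort and 30 to 33 over three cohorts. With an assumed probability p that a vaccinee has a qualifying Grade 3 event, the chance that the rule is met is

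P(X ≥ 2) = 1 − (1 − p)^n − n·p·(1 − p)^(n−1).

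For n = 30 and p = 0.05: 1 − 0.215 − 0.339 = 0.446.

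| Assumed p | n = 10–11 | n = 30–33 |
|---|---|---|
| 2% | 0.02 | 0.12–0.14 |
| 5% | 0.09–0.10 | 0.45–0.50 |
| 10% | 0.26–0.30 | 0.82–0.86 |

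Moving a few events across the Grade 2/3 boundary is therefore enough to change whether the rule is met. The values of p are assumptions, because the document gives none.

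**The case against.** The defence has several good points.

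- **Sore arms.** A reader might infer that ordinary arm soreness treated with a simple drug would be graded 3. It would not. Injection-site pain, redness and swelling have their own rows in Table 4. The over-grading is confined to limb limitation from unlisted events, such as the muscle and joint pain named in the Risk and mitigation section.
- **The treatment clause does work.** Hospitalization clearly separates Grade 3 from Grade 2, and direct double-grading arises only with mild intervention. Grades 1 and 5 do not mention limbs, and Grade 4 also mentions threat to life. To say that severity cannot be graded consistently at all would go too far.
- **The primary endpoint.** A reader might infer that a primary safety component is compromised. Outcomes {12} defines the adverse-event component by the percentage and frequency of subjects with events, and that does not use Table 6 grades.
- **Other stopping rules.** A disabling non-limb event would not necessarily escape every rule. Separate rules cover SAEs, serious adverse reactions, ICU admission, high fever and death, and the severe non-serious rule cites no grade number. The relatedness condition narrows the triggers, and a false Grade 3 trigger leads to a safety review.
- **Desquamation.** Its Grade 2 entry may contain a stray comma. This is minor.

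What stands is the inconsistency. Saying that CTCAE governs does not resolve it: the article prints Table 6 as its scale, names a different source in Table 1, and gives no rule for overriding the table. Nor is it an omission left to a fuller document, since the printed text conflicts with itself and with Table 4.

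**Conclusion.** The point holds as an internal inconsistency in Table 6. Grade 3 starts below the Grade 2 ceiling, so mild or moderate limb limitation with mild intervention meets both, and moderate limitation with fuller treatment is called severe. Treated non-limb events have no literal grade from 1 to 4. The consequence runs through the Grade 3, Grade 4 and severe-reaction triggers and falls mainly on severe, non-serious events without their own row in Tables 4 or 5.

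The conclusion rests on reading the limb and treatment clauses as joint conditions and on Table 5 having no headache or chills row, as shown. The document does not allow the frequency of misgrading to be computed, and the trigger probabilities above are not estimates of it.

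**What to change.** The sponsor should reconcile Table 6 with Tables 4 and 5, with the grading sources named in Statistical methods {20a} and Table 1, and with the triggers in the Stopping rules section. The result should be a scale whose grades are ordered, mutually exclusive and usable for events that do not involve a limb, and the text should say which source prevails where they differ. The fatigue row of Table 5 already grades by interference with activities, so the protocol has non-limb wording to reconcile against. Which thresholds are right is for the sponsor to decide.

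The same edit should clarify the repeated desquamation entry in the Table 5 skin row, and should say whether severe in the non-serious reaction rule means Grade 3.

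The cost is edits to the tables and the matching eCRF completion guide, with no new data or visits.
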